### Safety

In a meta-analysis examining over 33,200 sessions of tDCS, no serious adverse events were identified [23]. Common side effects of treatment that occur in up to 50% of patients include mild-to-moderate skin erythema, itchiness, tingling at electrode sites, or mild headache [20,24]. Less commonly observed side effects that have been reported include tinnitus, nervousness, light-headedness, blurred or brighter vision, reduced concentration, nausea, mild euphoria, fatigue, insomnia, or constriction when swallowing. When they occur, these side effects are generally transient and of low intensity.

In patients with bipolar depression, tDCS may rarely induce a manic or hypomanic switch. In a randomized control trial evaluating the use of tDCS in bipolar depression, treatment-emergent affective switches were observed in 15% of patients; however, these did not meet the criteria for hypomanic or manic episodes and did not require hospitalization or treatment discontinuation [25].

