### Objectives

The main objective of this study is to compare the effectiveness of active versus sham tDCS in ameliorating depressive symptoms in participants with ultratreatment-resistant MDD. We have operationally defined ultraresistant MDD to include depression that has failed to remit despite the use of ketamine, ECT, or at least five previous antidepressant trials at clinically effective doses. The secondary objectives of the study are to compare the safety of active versus sham tDCS and their respective effects on the speech and language abilities of participants.

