### Outcomes

The primary outcome will be the change on the MADRS, a 10-item, validated, observer-administered scale of depression severity, which has been extensively used in trials of depression treatment [34]. Investigators will use a structured interview guide when administering the MADRS to improve inter-rater reliability [35].

Secondary outcomes will include the change on the Quick Inventory of Depressive Symptomatology (QIDS-SR-16), a 16-item, participant-administered scale of depression severity, and the World Health Organization Disability Assessment Schedule (WHODAS 2.0), a 12-item measure of functional impairment [36,37]. Cognitive impacts of treatment will be assessed using the Screen for Cognitive Impairment in Psychiatry (SCIP) [38]. The SCIP has been well validated as a tool for measuring cognitive change in patients with depression and other psychiatric illnesses; is brief and relatively simple to perform; and includes a verbal list learning task, working memory test, verbal fluency test, delayed learning task, and visuomotor tracking test. Exploratory analyses will investigate the effect of treatment on language abilities by change in performance on an auditory lexical decision task, in which participants must differentiate real from fictitious words [39,40]. An exploratory acoustic and semantic corpus analysis will also be conducted on the recorded entrance and exit interviews.

Treatment-related manic or hypomanic switches will be captured using the Young Mania Rating Scale, an 11-item observer-administered scale of mania intensity [41]. Other treatment-related side effects will be measured using a scale derived from a systematic review of tDCS-related adverse events [42]. This scale has the benefit of asking participants to comment on the relatedness of their symptoms to their treatment and may help to distinguish between the likely side effects of tDCS and symptoms participants had before the intervention. It has also been used in other randomized control trials evaluating tDCS [43]. In addition, side effects that may be secondary to concurrent medication use will be captured using the Frequency, Intensity, and Burden of Side Effects Rating Scale and the Patient-Rated Inventory of Side Effects Scale [44,45]. Side effects captured through the use of the aforementioned scales will be summarized in an adverse events form, with additional documentation completed on any adverse events deemed to be serious in nature.

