### Data Analysis and Sample Size Calculations

The primary and secondary efficacy outcomes will be analyzed using a mixed effects repeated measures ANOVA (analysis of variance), with the study group and time as fixed factors and participants as random factors, based on the intention to treat principle. Due to the wide variety of potential adverse events that can be captured, we will present this information as frequency data.

To detect a moderate effect size for the primary outcome, represented by a Cohen *f* of 0.25, with a power of 80% and significance ⍺=.05, we estimate that 60 participants will need to complete the protocol. This assumes a moderate correlation (*r*=0.3) between time points, using the power curves described in the textbook by Kirk [46]. As a study of this scope, in the ultraresistant MDD population, has not been performed before, we are unable to estimate the dropout rate. We plan to conduct an interim analysis after 30 participants complete the protocol. We will analyze the main effects of the treatment by presenting the significance of the time, treatment group, and interaction terms in the ANOVA. If there is a significant interaction, we will conduct posthoc comparisons between mean treatment and placebo outcome scores, at each time point, to characterize this effect further and will use the Tukey method to control the familywise error rate.

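### Safety is to be compared between arms, but the stated analysis is bare frequencies with no use of the T0 safety scores; for symptoms common at baseline this comparison is unbiased but needlessly imprecise

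*Protocol article*

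**What the plan says.** The Objectives section states: "The secondary objectives of the study are to compare the safety of active versus sham tDCS". In Data Analysis and Sample Size Calculations, the model is reserved for efficacy ("The primary and secondary efficacy outcomes will be analyzed using a mixed effects repeated measures ANOVA"), and the next sentence deals with safety: "Due to the wide variety of potential adverse events that can be captured, we will present this information as frequency data". No between-arm contrast and no use of baseline is stated for safety.

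The Outcomes section describes the instruments by presumed cause. The Young Mania Rating Scale is for switches. For stimulation, "Other treatment-related side effects will be measured using a scale derived from a systematic review of tDCS-related adverse events". For medication, "side effects that may be secondary to concurrent medication use will be captured using the Frequency, Intensity, and Burden of Side Effects Rating Scale", together with the PRISE. It adds that "Side effects captured through the use of the aforementioned scales will be summarized in an adverse events form". The relatedness question on the tDCS scale "may help to distinguish between the likely side effects of tDCS and symptoms participants had before the intervention".

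The Safety section of the Introduction gives erythema, itchiness, tingling and mild headache as the common effects. Its less common effects include nervousness and "reduced concentration, nausea, mild euphoria, fatigue, insomnia, or constriction when swallowing". Entry requires a MADRS score above 34 (Eligibility Criteria). Table 1 schedules the tDCS-AEQ, FIBSER, PRISE and YMRS at T0, T10, T20, T30 and T60.

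**The concern.** The objective is comparative, and the analysis is a description with no stated contrast. The reason given, that events are varied, is a reason to avoid many significance tests. It is not a reason to leave out by-arm differences with intervals, or to ignore the baseline scores.

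The protocol sees that symptoms may predate treatment, but the remedy it names is participant opinion. Its own Limitations section cites evidence that healthy volunteers could tell this kind of sham from active stimulation, so judged relatedness may follow guessed allocation. The measured T0 scores, which need no causal judgement, are given no stated role in safety.

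About four of the listed effects overlap with the illness. If most participants already have such a symptom at T0, a count of everyone reporting it on treatment consists largely of people who had it before, and that adds noise to the comparison of arms. A real difference in insomnia or fatigue would be harder to see, and an apparently reassuring table would carry less information than the data allow.

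**Working it through.** **The plan's own figure.** No figure is stated for safety. The 60 completers are sized on the primary outcome (Cohen *f* 0.25, *r* = 0.3, 80% power, alpha 0.05). A between-group repeated-measures calculation gives 58 with five time points and 62 with four, so 60 is reproduced. It matters here only because 1:1 allocation gives about 30 per arm.

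**Inputs.** n = 30 per arm (from the protocol). The remaining inputs are assumptions: T0 prevalence *b* of 50%, 70% or 80%, persisting on treatment; new onset *q* among those free of the symptom of 15% (active) and 5% (sham).

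**Formulas.**
- Raw on-treatment frequency: *b* + (1 − *b*)*q*
- New since T0, all participants as denominator: (1 − *b*)*q*
- Difference between arms, both counts: (1 − *b*)(0.15 − 0.05)
- 95% half-width: 1.96 × √[(p₁(1 − p₁) + p₂(1 − p₂))/30]

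**Results.**

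| T0 prevalence | Raw, active v sham | New, active v sham | Difference (both) | Half-width, raw | Half-width, new |
|---|---|---|---|---|---|
| 50% | 57.5% v 52.5% | 7.5% v 2.5% | 5 points | 25.1 | 11.0 |
| 70% | 74.5% v 71.5% | 4.5% v 1.5% | 3 points | 22.5 | 8.6 |
| 80% | 83% v 81% | 3% v 1% | 2 points | 19.4 | 7.1 |

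First row in full: raw, √[(0.575 × 0.425 + 0.525 × 0.475)/30] = √0.01646 = 0.128, times 1.96 = 0.251. New, √[(0.075 × 0.925 + 0.025 × 0.975)/30] = √0.003125 = 0.0559, times 1.96 = 0.110.

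**Only those free of the symptom at T0.** The difference is 10 points, on 30 × (1 − *b*) = 15 per arm at 50% and 6 per arm at 80%. The half-width is 1.96 × √[(0.15 × 0.85 + 0.05 × 0.95)/15] = 21 points, and 33 points with 6 per arm. Difference over half-width is 10/21.2 = 0.47, against 5/11.0 = 0.46 for new events among all 30 and 5/25.1 = 0.20 for raw counts. The subgroup shows a larger number but carries about the same information as the count of new events.

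**Two checks.**
- The expected new-event counts are small (30 × 0.075 = 2.25 and 30 × 0.025 = 0.75 at 50%), where the simple interval is too narrow. With Newcombe's score interval at the expected counts, the half-widths are about 24 (raw) v 15 (new) at 50%, and about 20 v 13 at 80%. The gain is smaller but remains.
- With larger assumed onset rates (40% v 10%), the difference is 18 points at 40% prevalence with half-widths of 24.8 (raw) and 17.5 (new), and 6 points at 80% with 18.0 and 10.9.

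**The case against.** The strongest reply is that this is condensed text. Frequency data does not exclude display by arm or comparison with T0, and definitions of treatment-emergent events usually sit in an analysis plan or full protocol that is not shown. Descriptive reporting with about 30 per arm is also defensible. Much of this stands: missing detail alone would be no finding. What remains is that the article makes a choice, gives a reason for it, sets it beside a comparative objective, and names relatedness as its aid for prior symptoms.

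Three stronger readings are tempting and are not supported:

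- *The safety objective cannot be met.* Frequencies by randomised arm are a valid descriptive comparison, and randomisation balances prior symptoms and medication effects on average.
- *Events will be sorted by the scale that recorded them, so a stimulation effect on the PRISE is filed under medication.* The link between instrument and cause is hedged in the text, all scales feed one adverse events form, and no table layout is stated.
- *Raw counts shrink a 10-point difference to 5, 3 or 2 points.* The 10 points apply only to those free of the symptom at T0. Counting new events among all participants gives the same 5, 3 or 2 points. The loss is in precision; the raw comparison is not biased.

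The unblinding evidence comes from healthy volunteers, and the protocol says its relevance to depression is unknown. Unblinding could also affect self-reported new symptoms, so the fix does not remove that risk; it only removes the extra step of causal judgement.

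**Conclusion.** The concern holds in a limited form. The stated analysis serves the comparative safety objective poorly for the roughly four listed effects that overlap with depression. For effects rare at T0, such as erythema and tingling, raw frequencies by arm lose little.

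Under the assumed rates, raw counts give intervals a little over twice as wide at 50% prevalence (25 v 11 points) and nearly three times as wide at 80% (19 v 7 points), for the same expected difference. With a score interval the ratio is nearer 1.5 to 1.6. The prevalences and onset rates are assumptions; the documents give none for this population. The equality of the two differences also rests on T0 symptoms persisting, and on ignoring worsening among those who already have them. If prior symptoms remit at different rates by arm, the raw count measures net presence and the new-or-worse count measures emergence, which are different quantities.

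Even with the fix, intervals of this width allow only a descriptive reading.

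**What to change.** In Data Analysis and Sample Size Calculations, replace the frequency sentence with wording such as: *Adverse events will be shown by randomised arm as the number and proportion of participants with a symptom new or worse than at T0 at any later assessment, whatever scale recorded it and whatever cause was attributed, with the risk difference and a 95% interval suited to small counts. Results may also be shown among participants free of the symptom at T0. Participant-rated relatedness will be reported descriptively.*

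In Outcomes, add that the scale on which an event was recorded does not determine its attributed cause.

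The cost is wording and some extra table columns; all T0 and later scores are already in Table 1. The small downside is a large number of intervals without multiplicity control, so the text should say that they are descriptive.

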### Data Collection

Measurements for most scales will be conducted at the beginning of the trial (T0), after every 10 sessions (T10, T20, and T30), and 1 month after trial completion (T60; Table 1). Trained psychiatrists, psychiatric residents, and/or medical students will complete all assessments. Data will be collected directly using the REDCap electronic data capture tools.

Recorded entrance and exit interviews will be stored in an encrypted database and have identifying information stripped from them on a rolling basis. This database may then be analyzed in future studies.

Participants will perform the auditory lexical decision task on tablet devices using a previously developed app. They will first answer questions on their age, handedness, native languages, other spoken languages, age at which they began to learn English, English-speaking countries they have visited, and whether or not they grew up in western Canada. They will then hear a series of 200 stimuli and must mark whether they think each stimulus is a real or fictious word. There are a total of 2000 words split into 32 different lists. Participants will perform this task before commencing treatment (T0), after each stimulation session (T1-30), and 1 month after trial completion (T60).

There are 3 validated versions of the SCIP. To prevent participants from improving their scores by way of repeated exposure, version 1 will be administered at baseline, version 2 after the 30 treatments are delivered, and version 3 at the 1-month postcompletion assessment.

**Table 1 table1:** Schedule of assessments.

Assessment			Timepoint								
			Enrollment and baseline^a^		Treatment period^b^						Follow-up^c^
			T0		T1-9; T11-19; T21-29		T10; T20		T30		T60

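### The stated 80% power fits a group main effect averaged over visits, and does not carry over to MADRS change under the planned group-by-time ANOVA when T0 is a time level

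*Protocol article*

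**What the plan says.** In the protocol article, Data Analysis and Sample Size Calculations, the calculation starts "To detect a moderate effect size for the primary outcome, represented by a Cohen" f "of 0.25, with a power of 80% and significance" level .05, and continues "we estimate that 60 participants will need to complete the protocol". The correlation follows: "This assumes a moderate correlation (*r*=0.3) between time points". The source given is a textbook's power curves. The same section plans a mixed repeated measures ANOVA with group and time as fixed factors. It will report the time, group and interaction terms, and it makes visit-by-visit comparisons conditional on a significant interaction. It does not say to which term the f of 0.25 belongs.

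Under Outcomes: "The primary outcome will be the change on the MADRS". No visit is named there. Under Data Collection: "Measurements for most scales will be conducted at the beginning of the trial (T0"), then after sessions 10, 20 and 30, and one month after completion. Table 1 shows the MADRS at all five of these points.

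**The concern.** With baseline kept as a level of time, change between the arms appears as group-by-time divergence. The group main effect is something else: the difference between the arms averaged over all visits, T0 included. Randomisation makes the expected difference at T0 zero, so a benefit that exists only after baseline is diluted in that average. If the 80% was computed for the averaged group term with a 0.5 SD difference at every visit, it is not the power of the planned tests for a 0.5 SD benefit that begins after treatment starts.

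This affects how the result will be read. The Introduction says that earlier trials in treatment-resistant depression were small, so that lack of efficacy and design limits could not be told apart. A null result here would be read as evidence against a moderate effect that the planned terms may often miss. Low power on the interaction also decides whether the visit-by-visit comparisons are made at all.

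**Working it through.** **Inputs from the protocol article.** f = 0.25; alpha = .05; N = 60 completers; 1:1 allocation, so 30 per arm; r = 0.3; five MADRS visits, four of them after baseline. **Assumptions added here.** F tests at the 5% level; compound symmetry with equal variance at all visits; differences in SD units of the MADRS score. With two equal groups f = d/2, so f = 0.25 is d = 0.5.

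**1. Reproducing the stated figure.** Group main effect over m visits: lambda = f² N m / (1 + (m − 1) r), with 1 and N − 2 degrees of freedom.
- m = 5: 0.0625 × 60 × 5 / 2.2 = 8.52; power 81.9%; 80% needs N = 58.
- m = 4: 0.0625 × 60 × 4 / 1.9 = 7.89; power 78.9%; 80% needs N = 62.

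The stated 60 lies between 58 and 62.

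**2. Is it an interaction calculation?** lambda = f² N m / (1 − r), with m − 1 and (N − 2)(m − 1) degrees of freedom.
- m = 5: 18.75 / 0.7 = 26.8; power 99.2%; N = 28 would do.
- m = 4: 15 / 0.7 = 21.4; power 98.0%; N = 32 would do.

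Other conventions for the interaction, with four or five visits, gave N from 40 to 194, and none gave 60. An interaction f of 0.25 is also a much larger effect. For a difference of zero at T0 and δ at the four later visits, f = 0.2δ, so f = 0.25 means δ = 1.25 SD.

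**3. Power of the planned terms when T0 is a time level.** Let d_t be the group difference at visit t and d̄ its mean over the five visits.
- Group term: lambda = (N/4) × 5 d̄² / (1 + 4r) = 15 × 5 d̄² / 2.2.
- Interaction: lambda = (N/4) × Σ(d_t − d̄)² / (1 − r) = 15 × Σ(d_t − d̄)² / 0.7.

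| Difference at T0, T10, T20, T30, T60 (SD) | d̄ | Σ(d_t − d̄)² | Group term: lambda, power | Interaction: lambda, power |
|---|---|---|---|---|
| 0, 0.5, 0.5, 0.5, 0.5 | 0.40 | 0.200 | 5.45, 63% | 4.29, 34% |
| 0, 1/6, 1/3, 0.5, 0.5 | 0.30 | 0.189 | 3.07, 41% | 4.05, 32% |

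In the first row the effective main-effect f is 0.40/2 = 0.20, not 0.25.

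**4. Detectable difference at N = 60.** For a constant post-baseline difference in the five-visit ANOVA, 80% power needs about 0.61 SD on the group term or 0.84 SD on the interaction.

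**5. Average of the four post-baseline visits, constant 0.5 SD.** The variance of the mean of four visits is (1 + 3 × 0.3)/4 = 0.475 in score-variance units.
- Raw mean: 0.5/√0.475 = 0.725; power 79%.
- Mean change from T0: variance 0.475 + 1 − 0.6 = 0.875; 0.5/√0.875 = 0.535; power 53%.
- Baseline-adjusted mean: variance 0.475 − 0.09 = 0.385; 0.5/√0.385 = 0.806; power 87%.

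For the building profile the mean post-baseline difference is (1/6 + 1/3 + 0.5 + 0.5)/4 = 0.375 SD. The baseline-adjusted test then has 0.375/√0.385 = 0.604, or about 63% power.

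**The case against.** The strongest reply is that the arithmetic is correct. The article's inputs do give about 60 for a recognised test, and the article does not say that T0 is a level of time. If the group term covers only the four post-baseline visits, a constant 0.5 SD has 79% power on raw scores and 87% with baseline adjustment. This stands: the problem is a mismatch between the powered quantity and the named outcome, and a trial of 60 can reach 80% under some analyses. The article describes neither of those two analyses, and names change as the outcome.

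A second reply concerns the variances. Entry requires a MADRS above 34, which should narrow the baseline spread, and the equal-variance assumption then understates power for change scores. If the baseline SD were half the follow-up SD (an assumed ratio), mean change over four visits would have variance 0.475 + 0.25 − 0.30 = 0.425 and about 83% power. This stands for a four-visit change analysis. It does not remove the dilution of the group term by a T0 level.

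A reader might go further and infer that power for the primary outcome is 36% to 51%. Those figures belong to a test at T30 alone: raw change, 0.5/√1.4, gives 36%; baseline-adjusted, 0.5/√0.91, gives 51%. The article specifies neither a single-visit test nor baseline adjustment, so it does not support that range as the power of its primary analysis. Finally, the cited power curves are not available here, so the claim that 60 fits only the group main effect is limited to the variants tried.

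**Conclusion.** The point holds in limited form. The 80% reproduces, among the standard variants tried, only for a group main effect averaged over four or five visits. It does not carry over to MADRS change under the planned group-by-time ANOVA if T0 is a time level. For post-baseline effects of up to 0.5 SD, the group term has about 63% (constant effect) or 41% (building effect), and the interaction about 34% or 32%. These figures rest on compound symmetry with r = 0.3, equal variances, 60 completers and no expected difference at T0. Neither an arithmetic slip nor a need for more participants is shown.

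**What to change.** Keep N = 60. In the sample size paragraph, name the ANOVA term and the visits that f = 0.25 refers to, and restate the power or detectable difference for that test. For the five-visit ANOVA as planned, the statement could be that 60 completers give 80% power for a constant post-baseline difference of about 0.61 SD (group term) or 0.84 SD (interaction), assuming r = 0.3 and compound symmetry.

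Alternatively, make the primary test the baseline-adjusted group difference averaged over the four post-baseline visits, using the T0 MADRS that is already collected. Power is then about 87% for a constant 0.5 SD at r = 0.3. The paragraph should add that it falls to about 63% if the effect builds to 0.5 SD only by T30.

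The cost of the first option is a less favourable published figure. The cost of the second is that one primary term must be fixed in advance. Neither needs extra patients or visits.

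### The plan presents time, group and interaction as the treatment analysis without saying which is the primary test or at which visit MADRS change is judged

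*Protocol article*

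**What the plan says.** The Outcomes section of the protocol article states: "The primary outcome will be the change on the MADRS". No visit is attached. Under Data Collection, most scales are taken at baseline (T0), "after every 10 sessions (T10, T20, and T30), and 1 month after trial completion" (T60), and Table 1 lists MADRS at all five points.

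Under Data Analysis and Sample Size Calculations, the efficacy model is a "mixed effects repeated measures ANOVA (analysis of variance), with the study group and time as fixed factors and participants as random factors". The treatment analysis is then described as follows: "We will analyze the main effects of the treatment by presenting the significance of the time, treatment group, and interaction terms in the ANOVA". A significant interaction leads to active-versus-sham comparisons at each visit with Tukey control.

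The sample size rests on an effect "represented by a Cohen *f* of 0.25", "with a power of 80% and significance ⍺=.05". On correlation: "This assumes a moderate correlation (*r*=0.3) between time points". The result: "we estimate that 60 participants will need to complete the protocol". The text does not say which ANOVA term the effect size describes.

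**The concern.** A superiority trial needs one result that makes it positive or not. Here three F tests are put forward together as the analysis of treatment, at a single stated alpha.

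- **Time** compares visits, not arms. Everyone enters with MADRS above 34 and continues usual care, so scores may well fall in both arms without any benefit of tDCS.
- **Group** compares the arms averaged over the modelled visits. If T0 is one of them, the average includes a visit before treatment at which the expected difference is zero.
- **Interaction** tests whether the arms change differently over time, but as an omnibus test without a stated direction or visit.

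If group is significant and interaction is not, or the reverse, the reader cannot tell from the article whether the trial succeeded. The choice could then be made after the data are seen. The Tukey step does not cover it, because it controls only the visit comparisons that follow a significant interaction.

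**Working it through.** **Inputs.** From the article: f = 0.25, alpha .05, power 80%, r = 0.3, 60 completers, 1:1 allocation (30 per arm), visits T0, T10, T20, T30 and T60. Assumed: equal variances (SD = 1), the same correlation r between all visits, no dropout. The number of modelled visits is m = 5 with T0 as a level, or m = 4 without it.

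**1. Which term does the stated 60 belong to?**

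Noncentral F, two groups:
- Group: λ = N f² m / (1 + (m−1) r), with 1 and N−2 df.
- Interaction: λ = N f² m / (1 − r), with m−1 and (N−2)(m−1) df.

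For group at N = 60 and m = 5, λ = 60 × 0.0625 × 5 / 2.2 = 8.52. For interaction, λ = 60 × 0.0625 × 5 / 0.7 = 26.79.

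| Term | m | N for 80% (even) | Power at N = 60 |
|---|---|---|---|
| Group | 5 | 58 | 81.9% |
| Group | 4 | 62 | 78.9% |
| Interaction | 5 | 28 | 99.2% |
| Interaction | 4 | 32 | 98.0% |

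The stated 60 is reproduced within two participants by the group term and not by the interaction.

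**2. False-positive rate if either treatment term counts.**

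For two independent tests, 1 − (1 − 0.05)² = 0.0975. A null simulation (40,000 trials, 30 per arm, five visits, r = 0.3) gave group 4.9%, interaction 5.0%, either 9.6%; on change scores, either was 9.8%. Under an assumed AR(1) correlation of 0.6 without a sphericity correction, either was 11.2%. The planned interim look is a separate matter and is not counted.

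**3. Dilution of the group term.**

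With two arms, f = 0.25 is a difference of 0.5 SD averaged over the modelled visits. Suppose the benefit is 0.5 SD at every post-baseline visit and T0 is a level of time. The averaged difference is then 4/5 × 0.5 = 0.4 SD. The variance of a participant's five-visit mean is (1 + 4 × 0.3)/5 = 0.44, so λ = 15 × 0.4²/0.44 = 5.45. Power is 63%, not 80%.

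**4. One contrast with baseline as covariate, N = 60.**

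- Post-baseline average: residual variance (1 + 3 × 0.3)/4 − 0.3² = 0.475 − 0.09 = 0.385.
- T30 alone: residual variance 1 − 0.3² = 0.91.
- λ = 15 × (difference)² / residual variance, with 1 and 57 df.

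The ramp below is 1/3, 2/3, 1 and 1 times 0.5 SD at T10, T20, T30 and T60. Its mean is 0.375 SD over the four post-baseline visits and 0.3 SD over all five.

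| Profile, 0.5 SD at T30 | Group term with T0 | Adjusted post-baseline average | Adjusted T30 |
|---|---|---|---|
| Constant from T10 | 63% (λ = 5.45) | 87% (λ = 9.74) | 51% (λ = 4.12) |
| Linear ramp to T30, then held | 41% (λ = 3.07) | 63% (λ = 5.48) | 51% (λ = 4.12) |

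The adjusted average exceeds the T0-inclusive group term for any profile with a nonzero mean effect. At r = 0.3 the ratio of the two λ values is (5/4)² × 0.44/0.385 = 1.79 whatever the shape. No such ordering holds for T30: it beats the group term under the ramp and loses to it under the constant effect.

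**The case against.** Presenting every term of a factorial ANOVA is ordinary reporting. The article never says that a significant group term or a significant interaction would alone make the trial positive, nor that the time term would be claimed as efficacy. This stands: 9.75% is conditional on an either-counts reading and is not a stated property of the plan.

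A reader might also infer that none of the terms addresses the primary question. The article does not support that. With T0 in the model, the interaction tests whether MADRS change differs between arms; on change scores, the group term tests the mean difference in change. The Tukey comparisons would then show when and in which direction the arms differ. The dilution likewise applies only if T0 is a level of time, which the article leaves open.

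Nor may one infer that a T30 contrast is simply more powerful. The article states no effect profile, and under a constant 0.5 SD benefit the group term has 63% against 51% for T30. Moving to T30 at 0.5 SD would need about 118 completers for 80% power under the same assumptions, so it would break the present sample-size basis.

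Finally, covariance structure and similar detail commonly sit in a full protocol or analysis plan that is not shown, and their absence here is no fault. What this does not answer is that the article itself sets out the treatment analysis as three undesignated terms and the primary outcome without a visit. One could read the interaction as the gate, since the follow-up hangs on it, but the sample size points to the group term.

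**Conclusion.** The concern holds in a limited form. The article does not fix which of group or interaction is the primary test, or the visit at which MADRS change is judged, and no multiplicity rule joins the two terms. The consequence is a false-positive rate of about 9.75% under equal correlation between visits, if success on either term is accepted, against the stated 5%. The mismatch between the sizing (60 fits group at 58 to 62, not interaction at 28 to 32) and the follow-up step makes the ambiguity material. With T0 as a level of time, a constant 0.5 SD post-baseline benefit leaves the group term with 63% power.

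These figures rest on r = 0.3, equal variances and 60 completers. The case for a single contrast rests on pre-specification and on the use of baseline as a covariate, not on a general advantage of any one visit.

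**What to change.** Before unblinding, name one primary active-minus-sham MADRS contrast at two-sided .05. Take it from a mixed model of T10, T20, T30 and T60 with group, visit, group-by-visit and baseline MADRS as covariate. Report the time term, the omnibus terms and the other visit results as secondary or descriptive.

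Two choices are defensible:
- **Post-baseline average.** This is closest to the group term on which 60 appears to rest. At 0.5 SD it gives 87% against 63% for a constant effect, and 63% against 41% for the ramp. It answers a question about the whole course including follow-up.
- **T30 difference.** This is the end of the 30 sessions and is easier to interpret, with T60 secondary. Power must be restated: about 51% at 0.5 SD with 60 completers.

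If the sponsor prefers to keep both group and interaction as routes to success, each needs about .025 (Bonferroni) or .0253 (Šidák).

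The cost is one paragraph of analysis wording and a revised power statement, with no new measurements. With the average, the target of 60 can stay. With T30, the sponsor must accept lower power, justify a larger effect or enlarge the trial. In either case it gives up the option of claiming success on another term.
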